#### Primary endpoint

2.10.1

The primary outcomes of this study will be changes in the frequency of panic attack and in the PDSS and PASS during the observation period (3 months) and follow-up period (1 month), analyzed in both groups. After baseline time, they will be tested at week 0, week 4, week 8 and week 12, and during the follow-up period.

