### Sample size calculations

2.13

Based on preliminary experiments, it is obtained that after treatment the Kuppermann index (MI) of the intervention group dropped 15.90 ± 2.71, while the control group dropped 13.84 ± 1.87, the population standard deviation S = 2.12, δ = 2.06. Given α = 0.05 bilateral, β = 0.1, power of test 1−β = 0.9, based on formula^[15]^: n = 2 × [(tα+t2β) × s/δ] × [(tα+t2β) × s/δ], calculating with trial and error method, we used table look-up: tα, ∞ = 1.96, t2β, ∞ = 1.282, then we obtained n = 23.66 ≈ 24. According to t table: t0.05(24 × 2−2) = 2.0129, t0.2(24 × 2−2) = 1.3002, we substituted it into the former formula and obtain n = 23.25 ≈ 24, the sample size was plateaued, and the attempts stopped, which means each group requires 24 samples, and 2 groups require 48 samples in total (n = 48). With the consideration of the maximum loss rate of follow up is 20%, we concluded that the total sample size is 60. According to HAMA Score (14 items contained), the sample size is 14 × 5 = 70. Take two parts above into consideration, the sample size is determined at 70.

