### Statistical analysis

2.14

Image data processing: using methods like independent component analysis (ICA) and function binding, applying professional software such as MRIcro for windows, Xjview 8.1, SPM 12 and MATLAB 5.1.

Statistical analysis technique: to apply a statistical test to the difference of prior-treatment and post-treatment, and to examine the curative effect difference within groups and among groups of all curative effect indexes. We will adopt the two-sided test for all statistical tests. It's considered that the tested differences are statistically significant if *P* less than or equal to 0.05. If *P* greater than or equal to .05, the tested differences are not statistically significant. Details are as following.

Measurement data: The *t* test will be adapted to run comparison among groups. When it doesn’t comply with the normal distribution, we will choose Wilcoxon rank-sum test. Similarly, we will run paired *t* test towards the difference of prior-treatment and post-treatment, and it will be changed into Wilcoxon rank-sum test while it does not comply with the normal distribution.

Enumeration data: We will use the Chi-square test, calibration Chi-square test, and Fisher exact method to run comparison among groups.

Ranked data: Wilcoxon rank-sum test will be applied to run comparison among groups and signed rank-sum test to run comparison within groups.

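### The between-arm test for each primary outcome is chosen by how normal the collected data look, so its effect measure (means or ranks) is not fixed in advance

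*Protocol article*

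**What the plan says.** Section 2.14 (Statistical analysis) sets out to test changes from before to after treatment and "to examine the curative effect difference within groups and among groups of all curative effect indexes". For measurement data the default is that the t "test will be adapted to run comparison among groups". For data that do not "comply with the normal distribution, we will choose Wilcoxon rank-sum test". The within-group comparison has the same kind of switch: a paired t test is the default, and "it will be changed into Wilcoxon rank-sum test while it does not comply with the normal distribution".

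Section 2.10.1 (Primary endpoint) names three primary outcomes, each as a change: panic-attack frequency, PDSS and PASS. Of their timing it says "they will be tested at week 0, week 4, week 8 and week 12, and during the follow-up period", which gives four post-baseline occasions. Section 2.10.2 puts HAMA and SCL-90 on the same schedule.

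The article does not say how normality is judged, at what threshold, or whether the decision is made per arm, per visit or once per outcome. Attack frequency is a count, but section 2.14 specifies no rate-based analysis for it.

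**The concern.** The two tests answer different questions. The t test concerns a difference in means. The rank-sum test concerns whether values in one arm tend to exceed those in the other. A rule that picks between them from the observed distribution leaves the hypothesis and effect scale of a primary outcome open until the outcome data are in hand.

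Two things are at stake. First, results for one outcome could stand on different scales at different visits and could not be read as a single course over time. Second, the analyst has room to choose, because the trigger is not defined. For attack frequency, the most directly clinical of the three, a rank test alone does not say by how much the attack rate differs.

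**Working it through.** **The plan's own arithmetic.** The article gives no figure for the switching rule. Its one calculation, in section 2.13, is for a t test of means on the Kuppermann index: 2 × [(2.0129 + 1.3002) × 2.12 / 2.06]² = 23.25, so 24 per group as stated. Then 48 / (1 − 0.20) = 60, and 14 × 5 = 70, both as stated. The planning is therefore on means, with 35 per arm. Nothing below changes the sample size.

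**Inputs for the check.** From the article: 35 per arm, four post-baseline visits, two-sided 5% level, t test or rank-sum test. Assumed, because the article does not say: Shapiro-Wilk at 5% in each arm at each visit, with the rank-sum test used if either arm fails. All runs have no treatment effect.

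**Step 1: exactly normal data.** With two arms each falsely failing 5% of the time, both pass with probability 0.95² = 0.9025. If visits were independent, at least one switch in four visits has probability 1 − 0.9025⁴ = 0.34; a switch at all four is negligible. Simulation with correlated visits (correlation 0.6, 1,500 trials) sent 9.3% of comparisons to the rank test. Both tests were used for the same outcome in 31.4% of trials.

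**Step 2: a PDSS-like change score.** Scores were rounded and bounded at 0 and 28, with an assumed baseline mean of 15 falling to 12, 9, 7 and 7 (1,500 trials). The rank test was used in 16.4% of comparisons, and the tests were mixed in 50.7% of trials.

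**Step 3: how far this depends on the unit of the check.** With one pooled check per visit, independent visits give 1 − 0.95⁴ = 0.19. With one decision per outcome, mixing is 0%, but the choice of test still depends on the data.

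**Step 4: panic-attack counts.** Assumed: Poisson counts with gamma-distributed variation between women, and post-baseline rates of 0.7, 0.5, 0.4 and 0.4 times baseline (400 trials per cell). A smaller gamma shape means more variation between women. For change in count, which is the stated outcome, each cell shows the share of comparisons sent to the rank test / the share of trials mixing both tests:

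| Baseline mean | Shape 1 | Shape 2 | Shape 5 | Shape 20 |
|---|---|---|---|---|
| 2 | 99% / 4% | 93% / 26% | 81% / 53% | 72% / 68% |
| 4 | 98% / 7% | 85% / 42% | 57% / 76% | 39% / 76% |
| 8 | 99% / 4% | 86% / 38% | 53% / 69% | 26% / 61% |
| 16 | 99% / 3% | 90% / 30% | 54% / 69% | 18% / 51% |

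The rank test is close to certain only when women differ strongly (shape 1). Elsewhere mixing is common. A second simulation with its own assumed means and dispersions gave about 47% to 99%, inside the range of this table. For raw counts rather than changes, the table's settings gave 46% to 100%.

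**Step 5: type I error of the two-step rule.** It was 5.5% with normal data (t test alone 5.4%, rank-sum alone 4.9%) and 5.2% with the PDSS-like score. Over all count settings it ran from about 4% to 7%. In the highest cell (6.6%) the rank-sum test alone gave 6.3% on the same data. With 400 trials of four visits the standard error is at least √(0.05 × 0.95 / 1,600) = 0.5 percentage points, and more with correlated visits. There is no material inflation.

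**The case against.** The strongest reply is that this is a condensed article of an exploratory trial, and an unseen SAP may define the normality check. It may also give effect estimates, confidence intervals and the handling of partly observed periods. Those items are fairly left to an SAP, and their absence here is not part of this point. The switch is different because it is stated. An SAP that follows it inherits it. Defining the check would remove discretion but not the dependence of the effect measure on the data.

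Several stronger readings are tempting, and the article does not support them:

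- **That the test is chosen separately at each visit.** Section 2.14 does not say so. The 31% rests on that assumption and falls to 0% if one decision is made per outcome.
- **That attack frequency will nearly always get the rank test.** The article gives no count data, and the outcome is a change, which is less skewed than a raw count. The range of 18% to 99% is too wide for that claim.
- **That an equal-variance t test conflicts with the pilot data.** In section 2.13 the intervention group's Kuppermann index "dropped 15.90 ± 2.71, while the control group dropped 13.84 ± 1.87", a variance ratio of (2.71 / 1.87)² = 2.1. But section 2.14 never says which form of t test is meant, the index is not an outcome of this trial, and no pilot size is given.
- **That false positives are inflated.** They are not; see the last step of the check. The two tests also disagreed about significance in only about 2% of simulated null comparisons.

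The low effect on error rates stands and limits how serious the point is. It does not settle which effect the trial will report.

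**Conclusion.** The point holds in limited form. Section 2.14 picks means or ranks for every primary outcome after the data are seen, by a trigger that it does not define. That rests on the article's text alone.

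Its size rests on assumptions. With a per-visit, per-arm Shapiro-Wilk check, one outcome would be tested on both scales in about 31% of trials with normal data and about 51% with a PDSS-like score. Change in attack counts would often, but not predictably, go to the rank test, and no rate-based analysis is specified here. The harm is an unfixed effect measure and analyst discretion. The plan should be changed, but this does not undermine the trial's error control.

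**What to change.** Delete the normality-dependent switch in section 2.14 and name one analysis per outcome.

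- **PDSS, PASS, HAMA and SCL-90:** one baseline-adjusted comparison of means at every visit, with robust standard errors and a 95% confidence interval. Keep the rank-sum test as a sensitivity analysis only.
- **Panic-attack frequency:** one log-link count model, either negative binomial or quasi-Poisson, with the choice named now. Include baseline frequency as a covariate, which keeps the link to the stated change from baseline, and log(days observed) as offset. Report the rate ratio with its 95% confidence interval.

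The cost is wording only, apart from needing days observed for each period. Sample size, visits and treatment do not change. One downside needs handling: the likelihood-ratio test from the count model can be slightly liberal at 35 per arm (about 7% to 8% in simulation), which is worse than the rule it replaces. Its P-value should therefore come from re-randomisation.

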### Randomization

2.7

Random numbers will be generated by PEMS 3.1, and made into random cards. Then the cards will be sealed in opaque envelopes, kept by designated personnel. There is a one-to-one correspondence between the registration of clinic patients and the serial number of the envelope which contains the random number. Based on the number of the envelope each patient gets, these 70 patients will be grouped into the intervention group and the control group at random, and each group will contain 35 samples.

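### For non-normal before/after measurement data, section 2.14 replaces the paired t test with the rank-sum test, which ignores the pairing; the signed-rank test belongs there

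*Protocol article*

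**What the plan says.** Section 2.14 (Statistical analysis) of the protocol article sets out tests by data type.

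- **Measurement data, between groups:** a t test; if the data are not normal, "we will choose Wilcoxon rank-sum test".
- **Measurement data, within groups:** "we will run paired *t* test towards the difference of prior-treatment and post-treatment". If normality fails, "it will be changed into Wilcoxon rank-sum test while it does not comply with the normal distribution".
- **Ranked data:** the rank-sum test between groups and, separately, "signed rank-sum test to run comparison within groups".

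The general rule is "We will adopt the two-sided test for all statistical tests", and a result counts as "statistically significant if *P* less than or equal to 0.05". The section applies the tests broadly: it sets out "to examine the curative effect difference within groups and among groups of all curative effect indexes". Section 2.7 (Randomization) states that "each group will contain 35 samples", and section 2.13 allows for up to 20% loss to follow-up.

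**The concern.** The rank-sum test compares two independent samples. Before and after values from one patient are usually correlated, and the purpose of a paired test is to use that correlation. The rank-based counterpart of the paired t test is the signed-rank test. For measurement data the plan instead names one fallback, the rank-sum test, for both the between-group and the within-group comparison. For ranked data it separates the two cases correctly.

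An analyst who followed the text would run the wrong test whenever a before/after comparison of measurement data failed normality. Attack frequency is a primary outcome and a count, so this could plausibly happen, although the article gives no data on its distribution. At stake are the within-arm P values: they would not hold their nominal 5% level, and real within-arm changes could be missed.

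**Working it through.** The plan states no figure for this point, so there is none to reproduce. The check has three steps.

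**1. Inputs**

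- Two-sided 5% level (section 2.14).
- 35 pairs per arm as randomised (section 2.7). With the 20% maximum loss (section 2.13), 35 × (1 − 0.20) = 28 pairs.
- Before/after correlation ρ: not given. Assumed 0.3, 0.5 and 0.7, with 0, 0.9 and −0.3 as bounds.
- Size of change and shape of distribution: not given for any primary outcome. Assumed shifts are 0.4 and 0.5 SD (on the log scale for lognormal data). Distributions are normal and lognormal.

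**2. Type I error of the rank-sum test on paired data**

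The rank-sum statistic is scaled by a standard deviation that is valid for independent samples. With pairs, and no true change, the variance of the standardised statistic is about 1 − ρ_s rather than 1, where ρ_s is the rank correlation between before and after. If the values are normal, or lognormal with ρ taken on the log scale, ρ_s = (6/π)·arcsin(ρ/2). The true size is then about 2·[1 − Φ(1.96/√(1 − ρ_s))].

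- ρ = 0.3: ρ_s = 0.288, √0.712 = 0.844, 1.96/0.844 = 2.32, size about 2.0%.
- ρ = 0.5: ρ_s = 0.483, √0.517 = 0.719, 1.96/0.719 = 2.73, size about 0.6%.
- ρ = 0.7: ρ_s = 0.683, √0.317 = 0.563, 1.96/0.563 = 3.48, size about 0.05%.

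Simulation with lognormal values (10,000 replicates) agrees closely:

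| Assumed ρ | Rank-sum, 35 pairs | Rank-sum, 28 pairs | Signed-rank, 35 pairs |
|---|---|---|---|
| 0 | 5.1% | 5.4% | 4.8% |
| 0.3 | 1.9% | 2.2% | 4.4% |
| 0.5 | 0.8% | 0.8% | 5.2% |
| 0.7 | 0.1% | 0.2% | 4.5% |
| 0.9 | about 0 | about 0 | 4.9% |
| −0.3 | 8.5% | 7.8% | 5.0% |

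The signed-rank test stays close to 5% throughout. The rank-sum test does so only at zero correlation. It is conservative when the correlation is positive, the usual case, and would be too liberal if it were negative.

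**3. Power**

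| Assumed ρ | 35 pairs, 0.4 SD log-scale shift: rank-sum / signed-rank | 28 pairs, 0.5 SD fall: rank-sum / signed-rank |
|---|---|---|
| 0.3 | 34% / 44% | about 40% / 49–55% |
| 0.5 | 32% / 57% | about 40% / 62–69% |
| 0.7 | 28% / 79% | about 40% / 83–89% |

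In the last column, the upper end of each signed-rank range is for normal data and the lower end for lognormal data. The lognormal case is the more relevant, because the fallback applies only when normality fails.

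**The case against.** **The slip is obvious and its reach is small.** The ranked-data sentence shows that the authors know the within-group test. The fault touches only within-arm tests, only on measurement data, and only when normality fails. The between-arm comparison uses tests for independent groups, which is right, and the sample size is a two-group calculation. The trial describes itself as exploratory. All of this stands and sets the severity. It does not make the sentence correct.

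**The scales may never reach this fallback.** The article does not say whether PDSS, PASS, HAMA and SCL-90 count as measurement or ranked data. If ranked, they already receive the signed-rank test. This stands: one cannot say that every primary and secondary P value would be wrong. For the same reason, the two sentences conflict in approach but not literally, since they cover different data types.

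**The power loss may be irrelevant.** The only changes reported are the Kuppermann index falls in section 2.13: 15.90/2.71 = 5.9 and 13.84/1.87 = 7.4 standard deviations of change. If before and after SDs are equal, the smaller one equals 5.9 × √(2(1 − ρ)) raw SDs: 5.9 at ρ = 0.5, about 4.5 at 0.7 and 2.6 at 0.9. With effects that large, either test would reject almost always. The Kuppermann index is not a primary outcome here, so this does not settle the matter, but it does show that the power figures are illustrations.

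**A stronger reading to avoid.** Because section 2.14 tests change within groups, both arms are treated and entry requires HAMA ≥ 14, a reader might infer that the plan takes within-arm significance as proof of efficacy and so mistakes regression to the mean for benefit. No sentence says so: section 2.14 also tests between groups, and the abstract speaks of comparing the two groups. Moreover, with positive correlation the wrong test makes a significant within-arm result less likely, not more.

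**Conclusion.** The point holds in a narrow form. Section 2.14 names a test for independent samples where a paired test is needed, and nothing else in the article corrects it. The consequence is limited to within-arm before/after tests on measurement data that fail normality; the between-arm analysis and the sample size are unaffected.

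For the positive correlations assumed here, the nominal 5% test becomes a 2% to 0.1% test, so the harm is lost power and not false claims. The direction follows from ignoring a positive correlation. The amounts depend on the assumed correlation, shift and distribution, none of which the document supplies. Severity is minor to moderate: a stated rule is wrong, but it is peripheral to the randomised comparison.

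**What to change.** In the measurement-data paragraph of section 2.14, in the sentence on before/after differences, replace 'Wilcoxon rank-sum test' with 'Wilcoxon signed-rank test'. Leave the between-group fallback as it is. If the full protocol or the analysis plan carries the same sentence, make the same change there.

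The cost is one test name. Data collection, sample size and trial conduct do not change.

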### Quality control

2.15

All the investigators have been trained well to follow the trial's procedure and acupuncturists are instructed to give acupuncture treatment merely. Any other treatment or counseling is forbidden. To ensure the quality of the study, clinical monitors will arrange specialized staff to check the process of the trial and the details of medicine use. Additionally, monitors nominated by the principal investigator will verify the accuracy and validity of the original data which should be uploaded in time and accompanied with text summaries. Regular meetings will be organized to handle the difficulties and problems emerging during the study.

## Discussion

3

PD is also known as the acute anxiety attack (AAA), one of the main patterns of manifestation of anxiety disorder.^[16]^ Repeated outbreaks of panic, tachypnea, dizziness, palpitation, tremor, and sweating are its common symptoms. Modern medicine towards perimenopausal PD has a bunch of disadvantages, for example, hormone replacement therapy could increase the risk of higher morbidity of endometrial cancer, breast cancer, and colorectal cancer. Non-hormonal medication therapy may lead to nausea and vomiting, dizziness and headache, weakness and tremor, the change of weight. More importantly, low efficiency and high relapse are the biggest problems. In recent years, therapy combining CBT with pharmacotherapy has become a hot research area of treating PD. However, it still cannot solve these problems. These existing treatments have either little effectiveness or many side effects. Because many patients are dissatisfied with current treatments, the demand for acupoint catgut embedding is increasing. ‘Keep it for a long time to cure chronic diseases’ is the theoretical guidance of acupoint catgut embedding therapy. Based on traditional acupuncture technique, this therapy is developed by using modern technology. It takes advantage of the stimulation of acupoint via physicochemical change of the suture in the human body. It is a comprehensive regulative process. However, well-designed clinical trials on the effectiveness and safety of this therapy for perimenopausal PD are not available.

This study aims at proving the clinical effect and safety of acupoint catgut embedding. Meanwhile, with the help of fMRI and 1H-MRS, investigating the pathogenesis and physio-pathology characters by revealing neural activity and amino acid metabolism of perimenopausal PD patients is a significant goal as well. There are many studies showing different mechanisms in this disease. Our laboratory runs a variety of researches aiming at the GAMA mechanism in long terms. In this mechanism, free amino acid is an iconic index. And study has also shown the changes in fMRI images of perimenopausal PD patients.

Based on structural data from human and animal researches, brain-imaging studies have identified a network of structures that constitute the neural circuitry for emotions, including the amygdala, cingulate, insula and prefrontal cortex. They interact to distinguish the emotional significance of stimulations, to generate and regulate affective states further.^[17,18]^ Amygdaloid nucleus is described as the “fear center” of the brain or the core of “fear network”.^[19]^ Studies have shown that PD patients have an excessive activity of the amygdaloid nucleus and Hypothalamus-Pituitary-Adrenal axis (H-P-A axis). With the improvement of the disease, the activity of amygdaloid nucleus tends to be normal. The prefrontal cortex participates in emotional processing. Anterior cingulate cortex is closely related to mood and self-control.^[20]^ As the connecting hub, insular lobe connects with the anterior cingulate cortex, amygdaloid nucleus, prefrontal cortex and other tissues which also form the circuit. Insula hyperreactivity is associated with processing negative emotional information,^[21–23]^ threat-relevant cues and symptom severity.^[24]^ Structural phase studies found abnormal volume of insula gray matter, anterior cingulate cortex and amygdaloid nucleus occur in PD patients. Functional phase studies revealed that abnormal activities of amygdaloid nucleus, anterior cingulate cortex and prefrontal cortex lead to cognitive loss and predictive anxiety,^[25,26]^ suggesting the close connection between the occurrence and development of PD and neuro-anatomic structures.

In neuroimaging researches with CBT therapy, the most consistent findings regarding response to treatment were observed in the amygdala, insula, hippocampus and anterior cingulate, so they can be seen as relevant predictors of treatment response in anxiety disorders.^[27]^ After successful treatment with CBT, changes of brain activation in cortico-limbic structures have been discovered, particularly a inhibitory functional coupling between anterior cingulate cortex and amygdala concerning the response to treatment.^[28]^ Studies have shown that the precuneus and amygdaloid nucleus in patients with PD are related to anterior cingulate and negatively correlated with γ-GABA levels in the anterior cingulate.^[29]^ Neurological imaging studies have shown that Glutamate and GABA are the most important amino acid neurotransmitters, maintaining brain's excitement and inhibition, mediating conduction of more than 90% of brain's nerve. Combining with the outstanding disruptions in amino acid metabolism of OVX rats,^[13]^ we hypothesize that the metabolic disorder of amino acid, more accurately the imbalance of Glutamate-GABA caused by GABA's content decreasing, causing the excitatory and inhibitory imbalance of brain function, maybe the main etiological agent of perimenopausal PD.^[30]^

Early studies have shown the advantage of our study that acupoint catgut embedding has a significant effect on perimenopausal PD without side effects.^[31,32]^ Many previous studies are lack of enough indexes to reveal and measure the functions of the treatment.^[33,34]^ But our study will include credible scales and imaging changes of fMRI and 1H-MRS as persuasive evidence. Unfortunately, at present the syndrome differentiation of TCM is not certain yet. Diagnostic criteria and curative effect evaluation have no unified standard. All these factors restrict our research.

In conclusion, the results of this trial are expected to provide evidence for the effectiveness and brain correlates of acupoint catgut embedding treatment for perimenopausal PD. To reveal the pathogenesis and physio-pathology characters of perimenopausal PD with the help of fMRI and 1H-MRS is another expectation. We believe the outcome will exert a positive effect on acupoint catgut embedding treatment for perimenopausal PD.

